**Fig. 1 Fig1:**
[figure not shown]
Standard Protocol Items: Recommendations for Interventional Trials (SPIRIT) figure of enrolment, interventions and assessments

### Study procedures

Recruiting clinicians will be consultants in emergency medicine who currently use bolus propofol as sedation. They have a valid Good Clinical Practice Certificate. They are responsible for obtaining consent from patients and delivering the TCI propofol as per the flowsheet (Additional file 4). The clinicians have received aditional training in TCI propofol by an experienced anaesthetist (author MS). The recruiting clinician will be solely responsible for the administration of TCI propofol but not in the reduction of the anterior shoulder dislocation.

Potential participants presenting to the emergency department with a suspected shoulder dislocation will receive a patient information sheet in addition to their standard clinical care. On confirmation of a shoulder dislocation, they will be screened against the inclusion criteria by clinical staff within participating emergency departments.

Where a patient satisfies these criteria, the trained clinician, if on duty, will liaise with the clinical team to establish whether or not the patient is eligible for enrolment based on the formal inclusion and exclusion criteria detailed in the protocol.

In line with the current best practice [2], a minimum array of patient monitoring will be prescribed: 3-lead electrocardiogram, non-invasive blood pressure, peri pheral oxygen saturation and end-tidal carbon dioxide monitoring. There will be one clinician responsible for sedating the patient and another clinician undertaking the reduction. The sedating clinician will be assisted by a skilled assistant, normally an emergency department nurse. This is already undertaken as routine in all patients undergoing procedural sedation [2]. In addition, all patients will receive supplemental oxygen (via nasal cannulae at 4 L min^−1^) for the duration of the sedation episode.

Following patient enrolment, the TCI sedation flow sheet (Additional file 4) will be followed. The patient can receive morphine analgesia as long as it is administered at least 20 min before commencement of sedation. The dose and time of administration of morphine will be recorded.

The patient’s physiological parameters including heart rate, blood pressure and end-tidal carbon dioxide levels will be recorded prior to the administration of sedation and every 3 min until 15 min post reduction; thereafter, these will be recorded on a 15-min basis until full recovery. Likewise, the peripheral oxygen saturation will be recorded except with increased frequency, at 1-min intervals until 15 min post reduction upon which time they will be recorded on a 15-min basis. The non-invasive blood pressure will be obtained by measuring the posterior tibial pressure as we will be unable to use either arm owing to the dislocation and the TCI. When the patient’s modified observer’s assessment of alertness/sedation score (Additional file 5) reaches the target of 3, it will be recorded every 3 min until the procedure is complete. A patient-reported pain score for the procedure will be obtained after full recovery (Additional file 3).

Patients will be consented for the procedure and inclusion in the study by the responsible clinician. Written consent for use of the patient’s information and administering the propofol via TCI route as opposed to the standard bolus administration will be obtained pre-procedure.

Written consent will be sought from the patient to allow usage of their data collected during their stay in the ED and for administering the propofol via the TCI route. The procedure to relocate the shoulder and sedative agent being used would be the same regardless of their inclusion or exclusion in the study; it is only the method of administering the propofol that differs. The patient will be asked to sign the patient consent form that will then be counter signed by the responsible clinician. The patient will retain one copy of the signed consent form, and a further copy will be placed in the patient’s medical records whilst the original will be retained by the principal investigator.

The right of the participant to refuse to participate without giving reasons must and will be respected. All participants are free to withdraw at any time from the study without giving reasons and without prejudicing further treatment. Any data collected that is additional to the routine will be destroyed.

For each patient, a number of demographic, clinical and physiological parameters will be collected via clinical information systems and previous healthcare records.

### Data collection and management

A standardised data collection sheet will be utilised to record information for each patient enrolled in the study. The data collection sheet will be our source document. All data entered on the data collection sheet is hand written, and the information transcribed from a screen. On completion of the data collection sheet, they will be signed and dated. These will be maintained in an investigator file to be secured in a locked office within the study site. Information recorded on the data collection sheet will be recorded in a database located on a secure server.

Required data, other than that recorded at the time of sedation, will be retrieved from existing clinical IT systems and by review of the patient’s hospital notes. It is the principal investigators responsibility to ensure that all data is handled in a confidential fashion and in compliance with the protocol, local policy and statutory requirements.

The following is a non-exhaustive list of variables that will be recorded for each enrolled patient:AgeGenderED length of stayED discharge destinationMechanism of shoulder dislocationNumber of previous presentations following anterior shoulder dislocationPre-sedation physiologyTime of verbal and written consent

### Planned analysis

The plan of analysis for study data will be designed with the assistance of a biomedical statistician from the University of Strathclyde. Descriptive statistics will be presented.

Following the completion of this feasibility study, we plan to proceed to an RCT. The primary endpoint for our multi-centre RCT will be the incidence and severity of adverse events.

### Ethical approval and amendments

Ethical and amendment approval were obtained from the West of Scotland Research Ethics Committee 5, reference number 17/WS/0020 on 24 January 2017.

### Patient confidentiality

The principal investigator will preserve the confidentiality of participants taking part in the study in line with the Data Protection Act. Data held centrally by the principal investigator will be anonymised were practical and identified by a unique code. Documents that are not anonymised, such as signed informed consent forms, will be kept in a strictly confidential file by the principal investigator.

### Adverse event reporting

A serious adverse event occurring to a research participant will be reported to the main REC within 15 days of the chief investigator, or designee becoming aware where in the opinion of the chief investigator the event was related and unexpected. They will be reported as outlined in the ‘Safety and Progress Reports Table (non-CTIMPs) for UK health departments’ RES version 2.1 05.06.2015’.

### Protocol deviation reporting

A protocol deviation is any departure from the approved protocol. All deviations will be recorded and reported to the sponsor. Prospective protocol deviations will not be authorised by the sponsor unless the deviation is necessary to eliminate an immediate hazard.

### Publication policy

All publications and presentations relating to the study will be authorised by the chief investigator. Authorship will be determined according to the internationally agreed criteria for authorship (www.icmje.org). Our sponsor will review all documents prior to publication.

## Discussion

Research in emergency medicine is challenging owing to the unpredictable nature of the specialty and paucity of research support [31]. In the context of this challenging environment, a decision will be taken as to whether recruitment is adequate to allow progression to a randomised controlled trial. All observational studies have potential bias, and the results should generally not be used to change practice. The results of observational studies can be used to inform the development protocols for randomised clinical trials. The purpose of this study is to determine whether TCI propofol has the potential in terms of patient satisfaction to offer an alternative method for procedural sedation in the emergency department. The chosen primary endpoint of patient satisfaction scores will be inherently less prone to bias as patients are unlikely to have a bias for procedural sedation. In order to progress to a randomised control trial of TCI propofol against bolus propofol, TCI propofol would have to be no worse than standard bolus propofol in terms of patient satisfaction and also offer the potential of improved patient safety to be an acceptable clinical alternative for procedural sedation.

The purpose of the future multi-centre randomised trial is to compare the safety of propofol sedation, delivered via a target-controlled infusion, in comparison to that of usual bolus administration for the relocation of acute traumatic shoulder dislocation in adult patients in the emergency department. Our primary endpoint for that RCT will be the incidence of adverse events as recorded on the World SIVA adverse event sedation reporting tool [33]. We believe that the results will be generalisable to other painful procedures in the emergency department.

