**Methods:**

This study will recruit in four emergency departments in Scotland, UK. Patients aged 18–65 years with anterior shoulder dislocation, weighing ≥ 50 kg and fasted ≥ 90 min, will be screened. Recruited patients will undergo emergency reduction of a dislocated shoulder facilitated by procedural sedation utilising TCI of propofol.

The widespread adoption of TCI propofol by emergency departments will require evidence that it is safe, potentially effective, patient centred and a timely method of providing procedural sedation. The primary endpoint will be acceptability measured by patient satisfaction. The secondary endpoints will include incidence and severity of adverse events, number of shoulder reduction attempts, nursing opinion of patient experience, patient’s reported pain score and time from commencement of TCI propofol sedation to desired sedation level.

The study will be open for recruitment from April 2017 to December 2018.

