### Study rationale

There exists continued controversy over the use of propofol in ED PSA; this is despite its widespread existence in clinical practice for at least a decade. These concerns are not limited to the ED setting and are primarily related to the pharmacological properties of the drug itself and its potential for harm. The bolus administration of propofol, aimed at a target of sedation, offers several advantages over more traditional agents, yet these advantages are also its limitations. The use of a target-controlled infusion makes titration of propofol easier with fewer adjustments, thus potentially reducing the incidence of adverse incidents.

The incidence of adverse events using bolus propofol versus TCI propofol in the emergency department will be recorded in the future randomised controlled trial (RCT). This current feasibility study is needed first before a main trial in order to provide evidence that TCI is safe, potentially effective, patient centred and a timely method of providing procedural sedation. It will also provide information about recruitment to ensure that the randomised controlled trial can be adequately powered.

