### Progression

Progression to a multi-centre randomised control trial will require evidence of the ability to adequately recruit and that it is safe, potentially effective, patient centred and a timely method of providing procedural sedation.

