## Methods

### Study design

Multi-centre feasibility study

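### Progression is made to depend on satisfaction being no worse than with bolus propofol, which a TCI-only study with no bolus satisfaction data cannot show

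*Protocol article*

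**What the plan says.** **Condition.** The Discussion says that, for a randomised trial to follow, "TCI propofol would have to be no worse than standard bolus propofol in terms of patient satisfaction". It adds that TCI must "also offer the potential of improved patient safety to be an acceptable clinical alternative for procedural sedation". The two limbs are joined, so both are required.

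**Design.** Study design reads, in full, "Multi-centre feasibility study", with no comparator named. The Abstract says "Recruited patients will undergo emergency reduction of a dislocated shoulder facilitated by procedural sedation utilising TCI of propofol", and Study procedures describes TCI delivery only. Patient satisfaction on a VAS is a primary endpoint, listed without a reference value. Planned analysis promises descriptive statistics.

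**Where the bolus comparison is placed.** Study rationale says: "The incidence of adverse events using bolus propofol versus TCI propofol in the emergency department will be recorded in the future randomised controlled trial".

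**Progression elsewhere.** The Progression section opens: "Progression to a multi-centre randomised control trial will require evidence of the ability to adequately recruit". It goes on to safety, potential effectiveness, patient-centredness and timeliness, and does not mention bolus. The Abstract's Discussion paragraph asks for patient acceptability and adequate recruitment. Planned analysis says "Following the completion of this feasibility study, we plan to proceed to an RCT".

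**The concern.** A progression rule has to be answerable from what the study measures. The satisfaction limb asks how TCI compares with bolus, and this study measures only TCI. At the end the team would have a satisfaction distribution for TCI and nothing in the article to compare it with. They would have to set the limb aside or judge it against experience not recorded in the article, possibly after seeing the scores.

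The limb concerns a primary endpoint, and the Discussion presents satisfaction as the purpose of the study. The article also gives a non-comparative basis for progression in the Abstract and in Progression. Two readers with the same data could therefore disagree on whether the satisfaction requirement had been met.

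**Working it through.** **1. The plan's own number.** Sample size rationale gives 13 patients per week for 86 weeks, then divides by 5 (consent), by 5 (trained consultants) and by 2 (consultant hours):

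- 13 × 86 = 1118
- 1118 / 5 = 223.6 (stated as 224)
- 223.6 / 5 = 44.7 (stated as 45)
- 44.7 / 2 = 22.4 (stated as about 22)

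The figure reproduces. The same section also gives the total as 1116, which changes nothing here (1116 / 50 = 22.3). The target is at least 20. All these patients receive TCI.

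**2. Can the satisfaction limb be estimated?** The quantity is mean(TCI) − mean(bolus), with variance s²(TCI)/n(TCI) + s²(bolus)/n(bolus). Here n(TCI) is about 22 and n(bolus) = 0, so neither the difference nor its variance exists. A fixed external value could stand in for the bolus mean, but the article gives none. Recruiting more TCI patients would not help.

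**3. What the single arm can give.** The 95% half-width for one mean, in SD units, is t(0.975, n−1)/√n:

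- n = 20: 2.093 / 4.472 = 0.468 SD
- n = 22: 2.080 / 4.690 = 0.443 SD

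The article states no SD. Assuming a 100-point scale:

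| Assumed SD | n = 20 | n = 22 |
|---|---|---|
| 10 | ±4.7 | ±4.4 |
| 20 | ±9.4 | ±8.9 |
| 30 | ±14.0 | ±13.3 |

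**4. If an external bolus value were named.** Treat that value as known, take one-sided 2.5% and 80% power, and assume TCI truly equals it. Then n = (SD × (1.960 + 0.842) / margin)². With SD 20 and margin 10 this is (5.604)² = 31.4, so 32 patients. For SD 10, 20 or 30 and margin 5, 10 or 15 the range is 4 to 283. Only three of the nine combinations need 22 or fewer: SD 10 with margin 10 (8) or 15 (4), and SD 20 with margin 15 (14). SDs and margins are assumptions.

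**5. The safety limb.** The Background cites airway complications in 5.0 to 9.4% of emergency department propofol sedations. With 0 events in 22, the exact two-sided 95% upper limit is 1 − 0.025^(1/22) = 15.4%. The chance of 0 in 22 is 0.95^22 = 32% at a true rate of 5.0%, and 0.906^22 = 11% at 9.4%. So 22 patients could not demonstrate improved safety. The limb asks only for potential, however, and it has published figures to be set against.

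**6. The progression statements side by side.**

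| Place | Basis for progression | Needs bolus satisfaction data? |
|---|---|---|
| Abstract, Discussion paragraph | Acceptability and recruitment | No |
| Progression | Recruitment, safety, potential effectiveness, patient-centredness, timeliness | No |
| Planned analysis | Intention to proceed | No |
| Discussion | No worse than bolus on satisfaction; potential for better safety | Yes |

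**The case against.** The best defence is that one Discussion sentence is being read as the operative rule. The article has a section headed Progression; its criteria, the Aim and the Abstract can all be addressed from TCI patients alone. That is true and limits the damage, but the sentence is worded as a requirement, so it conflicts with the rest.

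A second defence is that a benchmark or margin may sit in a full protocol or analysis plan that is not shown. This stands in part: their absence from a condensed article is not a fault in itself. But no later document can turn a TCI-only study into a source of bolus scores. At most it could import an outside value, which this article does not mention.

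Four stronger readings are tempting, and the documents do not support them:

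- *The safety limb fails in the same way.* It asks for potential only. The Background gives reference rates and also cites a randomised trial in endoscopy with fewer respiratory and cardiovascular events under TCI than under bolus.
- *Planned analysis commits to the trial whatever happens.* It states an intention; the Abstract, Progression and Discussion all attach conditions.
- *Any result would justify progressing.* Recruitment, safety, effectiveness and timeliness still have to be satisfied under Progression.
- *The study as a whole cannot inform progression.* Recruitment and absolute satisfaction with TCI remain validly estimable.

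**Conclusion.** The point holds for the satisfaction limb. As written, the Discussion sets a comparative condition that the study's own data cannot answer: about 22 TCI patients, 0 bolus patients and no reference value in the article. It is also inconsistent with the non-comparative criteria in the Abstract and in Progression.

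This conclusion depends on the design alone and on no assumed SD or margin. The precision of ±0.47 to ±0.44 SD follows from 20 to 22 patients with a t-based interval; its translation into VAS points is illustrative.

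The matter should be fixed, but it is not fatal. No patient's treatment, data item or descriptive summary is affected. What changes is the conclusion the study may draw on a primary endpoint.

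**What to change.** Delete the no-worse-than-bolus satisfaction condition from the Discussion and leave that comparison to the randomised trial. Replace it with an absolute criterion on the TCI satisfaction VAS, either a mean or a proportion of patients at or above a cut. Fix the cut before the data are examined, report the result with a 95% confidence interval, and choose the cut with the precision above in mind. Suggested wording:

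*Alongside the criteria under Progression, patient satisfaction with TCI propofol must reach a pre-set acceptability level on the VAS, reported with its 95% confidence interval. Comparison with bolus propofol is left to the randomised trial.*

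Put the same rule in the Progression section so that the two places agree. The safety limb can stay as a statement of potential.

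If the team prefers to keep a comparative statement, it would need a named external bolus satisfaction value, its source and a margin; step 4 of the working shows how often 20 to 22 patients would be too few. Go, amend and stop bands are optional.

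The cost is wording only, with no extra patients or data. Trial status says recruitment is still open, which favours settling the cut now.

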## Trial status

The trial is currently open for recruitment. The Standard Protocol Items Recommendations for Trials (SPIRIT) checklist has been added as Additional file 6.

## Abbreviations

ASA: American Society of Anesthesiologists
ED: Emergency department
OAA/S: Observer’s Assessment of Alertness/Sedation Scale
PSA: Procedural sedation and analgesia
SIVA: Society for Intravenous Anaesthesia
TCI: Target-controlled infusion
VAS: Visual analogue scale
